6.3.23 CSF Cryptococcal Isolate Storage

CSF cryptococcal isolates must be obtained from all Cryptococcus-positive cultures. All CSF cryptococcal isolates should be stored as described in section 2 of the A5225/HiFLAC MOPS for future fluconazole susceptibility testing and sub-typing in a central laboratory.

6.3.24 PK Sampling (see section 10.0)

Section 10.2 contains specific collection and reporting requirements and should be consulted prior to any collection.

PK samples will be collected only from participants who receive **study-provided** fluconazole during Step 1. Participants who prematurely discontinue study-provided fluconazole prior to exiting Step 1 will not undergo PK evaluations at subsequent visits.

NOTE: Under the following conditions, the PK collection should be rescheduled to occur within 1 week.

- If the participant has missed any doses of fluconazole within the previous 3 days or on the day of collection
- If a participant taking EFV has missed any doses of EFV within the previous 3 days
- If a participant taking RIF daily has missed any doses of RIF within the previous 3 days or on the day of collection
- If a participant taking RIF less frequently than daily has missed any doses of RIF within the previous week

With the exception of the week 2 sample, the CSF collection, when an LP is clinically indicated, should also be rescheduled, when the collection of PK samples is postponed.

If it is not possible to reschedule the CSF collection to coincide with a rescheduled PK visit, a single PK sample should be collected within 1 hour of the CSF sample collection at the originally scheduled visit. If it is not possible to reschedule the PK visit, a single sample should be collected at the originally scheduled PK visit.

In addition, a single plasma sample for fluconazole levels will be collected at the time that Premature Treatment or Study Discontinuation evaluations are performed from all participants who prematurely discontinue the study or prematurely discontinue study treatment, except as noted in 6.2.4 for participants who are found to be HIV- and/or CM-negative.

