## 7.0 CLINICAL MANAGEMENT ISSUES

A5225/HiFLAC sites must follow the DAIDS Table for Grading the Severity of Adult and Pediatric Adverse Events Version 1.0, December 2004, which can be found on the DAIDS DAIDS RSC Web site: <http://rsc.tech-res.com/safetyandpharmacovigilance/>, for grading toxicities related to study treatment.

Toxicity management at non-US CRSs may require reliance on clinical symptoms, clinician judgment, and available laboratory markers, since alternatives to study-provided treatment may be very limited and baseline levels may be different from those in other settings. It is understood that treating physicians will provide whatever available treatment is considered best to protect patient safety and well-being; compliance with study requirements must not compromise such treatment.

This section provides guidelines for management of toxicities related to **study-provided** fluconazole. Management of toxicities thought to be related to ampho B will be according to local standard of care. Guidelines for use of ampho B and management of the most common toxicities associated with it are included in section 5 of the A5225/HiFLAC MOPS and may be consulted, at the discretion of the site investigator.

Participants who permanently discontinue either fluconazole or **any** ampho B**-based regimen** because of an AE should be followed closely until resolution of the AE can be documented.

In the subsections below, ‘interruption’ is used to mean a temporary discontinuation, while ‘discontinuation’ is used to mean a permanent discontinuation. If study-provided fluconazole is interrupted for longer than 3 consecutive days, it must be discontinued and the participant must immediately be treated according to local standard of care (SoC).

The A5225/HiFLAC core team must be notified via e-mail ([[contact]](mailto:[contact])) within 3 business days after premature discontinuation of fluconazole or ampho B in Step 1 or Step 2.

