### 10.2 Pharmacology Study Design

10.2.1 Single sample for fluconazole at week 2

Plasma: At week 2, all participants in fluconazole induction cohorts will have whole blood collected for drug concentrations of fluconazole. For participants taking fluconazole once daily, the collection should take place 15-33 hours after the last dose of fluconazole and prior to the next dose of fluconazole. For participants taking fluconazole twice daily, the collection should take place 8-16 hrs after the last dose of fluconazole and prior to the next dose of fluconazole. For participants taking fluconazole more frequently than twice a day, sites should attempt to make the collection at least 4 hours after the most recent dose. The plasma PK sample should be obtained within 1 hour (ie, before or after) of the CSF collection described below.

CSF: A CSF sample must be obtained from all participants described in the paragraph above.

The date and time of the administration of all fluconazole doses for the previous 3 days and the day of the study visit as well as the date and time of plasma and CSF sampling will be recorded on the CRF.

- - 1. Single sample for fluconazole in participants taking RIF or EFV

Plasma: Whole blood will be collected for fluconazole concentrations and concentrations of the concomitant drug from all participants in the 1600 mg and 2000 mg daily fluconazole cohorts who are taking RIF and/or EFV (with no concomitant NVP) during the induction step. This collection should take place at least 2 weeks after the initiation of co-administration of fluconazole with the concomitant drug. For participants taking fluconazole once daily, the collection should take place 15-33 hours after the last dose of fluconazole and prior to the next dose of fluconazole. For participants taking fluconazole twice daily, the collection should take place 8-16 hrs after the last dose of fluconazole and prior to the next dose of fluconazole. For participants taking fluconazole more frequently than twice a day, sites should attempt to make the collection at least 4 hours after the most recent dose. The plasma sample should be obtained within 1 hour (i.e., before or after) of the CSF when CSF is collected as described below.

CSF: In addition, a CSF sample will be obtained for drug concentrations (if an LP is performed for other clinical or study purposes) from all participants taking part in this PK collection.

The following will be recorded on the CRF:

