- date and time of all plasma and CSF samplings
- date and time of the administration of all fluconazole doses for the previous 3 days and the day of the study visit
- date and time of day (or actual or approximate time, if available) of all EFV doses for the previous 3 days and the day of the study visit (for participants taking EFV);
- date and time of day (or actual or approximate time, if available) for all RIF doses in the previous 3 days and the day of the study visit (for participants taking RIF daily);
- date and time of day (or actual or approximate, if available) for the last RIF dose including the day of the study visit (for participants taking RIF less frequently than daily).
  - 1. Single sample for fluconazole before and after dose reduction due to intolerability/toxicity

Plasma: All participants in the 1600 mg and 2000 mg daily fluconazole cohorts who require dose reduction of fluconazole due to intolerability/toxicity will have whole blood collected for fluconazole concentration at the time of the assessment of intolerability and prior to dose reduction. This sample can be obtained at any time during the induction step after the previous dose of fluconazole.

An additional sample will be collected at least 2 weeks after the dose reduction and while the participant is still taking the reduced dose. This sample may be obtained during a scheduled study visit. If the dose has resumed to full-dose, no sample should be taken for PK.

For participants taking fluconazole once daily, the collection should take place 15-33 hours after the last dose; for participants taking fluconazole, more frequently, the collection should take place 8-16 hrs after the last dose. For participants taking fluconazole more frequently than twice a day, sites should attempt to make the collection at least 4 hours after the most recent dose. The PK sample should be obtained within 1 hour (i.e., before or after) of the CSF sample described below is obtained.

CSF: In addition, a CSF sample will be obtained for drug concentrations from any participants involved in these PK collections for whom an LP is being performed for other clinical or study purposes.

For each sample, the date and time of the administration of all fluconazole doses for the previous 3 days and the date and time of blood and CSF sampling will be recorded on the CRF.

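### Section 6.3.24 by default reschedules CSF collection at a clinically indicated LP, by up to a week, when a PK draw is postponed for missed doses, and its exception does not name clinical need

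*Protocol*

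**What the plan says.** Protocol section 6.3.24 lists missed doses of fluconazole, efavirenz (EFV) or rifampin (RIF) that trigger postponement: "Under the following conditions, the PK collection should be rescheduled to occur within 1 week". It then carries the postponement over to CSF: "With the exception of the week 2 sample, the CSF collection, when an LP is clinically indicated, should also be rescheduled". The fallback begins "If it is not possible to reschedule the CSF collection to coincide with a rescheduled PK visit"; in that case a single PK sample is taken within 1 hour of the CSF collection at the original visit.

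Section 10.2 sets out the PK collections other than the routine week 2 one. For participants taking RIF or EFV, CSF is obtained for drug levels "if an LP is performed for other clinical or study purposes". For participants whose dose is reduced for toxicity, it is obtained from those "for whom an LP is being performed for other clinical or study purposes".

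Section 7.0, on clinical management, says that physicians will give the best available treatment and that "compliance with study requirements must not compromise such treatment". Section 1.4.2 lists the pharmacology objective as exploratory.

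**The concern.** The trigger in 6.3.24 is adherence in the days before the draw (for intermittent RIF, the week before), not the participant's condition. What it moves is CSF collection at an LP that someone has judged clinically indicated. Section 6.3.17 counts diagnosis, monitoring and relief of intracranial pressure among the LPs done as part of care. In cryptococcal meningitis, such a procedure should not wait for a drug-level sample.

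The exception makes this worse. It turns on whether rescheduling can be done, and an LP that is needed today can usually be booked for later in the week. A site that follows the text literally gets no prompt to ask whether it ought to be. What is at stake is the safety of a small group. The trial's estimates are not affected.

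**Working it through.** No power, alpha or sample-size figure is involved. The check is a comparison of texts, with simple arithmetic for the limits.

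1. **Does the CSF collection itself move?** The clause could be read as saying only that the postponed PK visit includes CSF if an LP happens to be indicated then. The next sentence does not fit that reading. It speaks of rescheduling the CSF collection to coincide with the new PK visit and, failing that, of collecting CSF at the originally scheduled visit. So the collection moves. Doing the LP on time and collecting the PK sample later would need a second LP for PK alone, which 10.2 does not provide for.

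2. **Could study-required LPs have been meant?** The words say clinically indicated. The other meaning would also fit badly with section 6.2.2, which allows ± 3 days for the week 4 to 10 visits. A week 4 collection planned for day 28 and moved the full week falls on day 28 + 7 = 35. The window is days 25 to 31, so it would be 35 − 31 = 4 days late.

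3. **How does this compare with 10.2?** There the LP leads and PK sampling follows. In 6.3.24 a postponed PK draw leads and the CSF collection follows. Section 10.2 does not discuss postponement, so the two are in tension without contradicting each other outright.

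4. **Does PK sampling need the rule?** Partly. Section 10.2 wants plasma within 1 hour of CSF, and sampling after missed doses gives a pair that is not at steady state. Moving both together preserves the pair. The plasma schedule itself is loose, however. For RIF or EFV, "This collection should take place at least 2 weeks after the initiation of co-administration of fluconazole with the concomitant drug". After a dose reduction, "An additional sample will be collected at least 2 weeks after the dose reduction and while the participant is still taking the reduced dose". Neither fixes a day, so a later plasma draw remains possible while the participant is still in induction (and, in the second case, still on the reduced dose).

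5. **Size of the delay.** Within 1 week means at most 7 days.

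6. **Who could be exposed?** All of the following must hold: a 1600 or 2000 mg cohort; RIF or EFV use, or a dose reduction; still in induction; a PK collection due other than at week 2; missed doses in the look-back period; and a clinically indicated LP outside a Progression of Symptoms visit. The collections in 10.2.4 and 10.2.5 are plasma only and do not count.

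7. **Ceiling.** Section 5.1 describes Stage 1 as completed. Schema Table 2 gives Stage 2 four cohorts of 24, one of them on ampho B: 96 − 24 = 72. Without the fluconazole plus flucytosine cohort, 72 − 24 = 48. These are enrolment ceilings. The number meeting every condition in step 6 is not given and would be a small part of them.

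**The case against.** The strongest reply is that urgent care is already protected. Under section 6.2.3, recurrence or significant worsening of CNS signs leads to the Progression of Symptoms work-up, where section 6.3.21 makes CSF collection mandatory. Section 6.3.17 expects clinical LPs throughout the study and asks only that they be recorded. Section 7.0 puts treatment first. The verb in 6.3.24 is advisory, and an investigator may fairly treat an LP that is needed now as one that cannot be rescheduled. Section 6.3.24 also sends sites to 10.2 before any collection, so the LP-led rule is read first.

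Much of this stands, and it keeps the point small. It does not remove the instruction. An LP for monitoring, or for persisting pressure without worsening, can fall outside the progression work-up. The principle in 7.0 sits in the section on toxicity management, and 6.3.24 does not refer to it. If the safe reading depends on a generous sense of not possible, it is better to write that reading down.

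The reply is also right that the rule serves a purpose: it keeps plasma and CSF paired at steady state. A reader might infer that the rule is pointless for PK. The documents do not support that.

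**Conclusion.** The point holds as a minor matter of safety wording and is a cheap improvement. As a default, 6.3.24 ties CSF collection at a clinically indicated LP to an exploratory PK schedule, with a delay of up to 7 days and an exception that does not mention clinical need. Other sections limit the harm but leave the sentence in place.

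This rests on reading the sentence together with its fallback, which shows that the collection moves, and on Stage 1 being closed to enrolment. The ceiling of 72 (or 48) participants is not an estimate of those affected.

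Three stronger readings are tempting and are not supported:

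- A reader might infer a direct contradiction with 10.2. That section says when CSF is taken for PK and is silent on postponement.
- A reader might infer that deteriorating patients would go without an LP. Sections 6.2.3 and 6.3.21 route them to a mandatory collection.
- A reader might infer bias in the culture endpoint. The week 2 sample is exempt from the rescheduling sentence, and nothing here shows an effect on later culture results.

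**What to change.** Replace the rescheduling sentence in 6.3.24 with:

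> A clinically indicated LP is not to be delayed for PK sampling; if the PK collection is postponed, collect CSF at the original time with a single plasma PK sample within 1 hour and record the missed doses.

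The fallback sentence that follows is then no longer needed for these LPs. Non-urgent study-required LPs can stay under the existing visit windows in 6.2.2. The argument here gives no reason to bar moving them.

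The change makes the protocol's own fallback the default, and 10.2 already requires recent dosing times to be recorded. Section 3.0 says that the protocol will be amended before Stage 2 opens, so the sentence can go into that amendment. The cost is a few plasma/CSF pairs outside week 2 that are not at steady state, for an exploratory objective.

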6.3.25 Stored Plasma

An additional blood sample for plasma storage must be collected as indicated on the SoE and stored for possible future microbiologic, immunologic, and virologic evaluations. See section 2 of the A5225/HiFLAC MOPS and/or the A5225/HiFLAC LPC for collection and storage instructions.

6.3.26 Stored Serum

A serum sample will be collected **as indicated on the SOE** and stored for possible microbiologic evaluations.

6.3.27 Stored Urine

A urine sample will be collected at entry and at a Progression of Symptoms visit and stored for possible microbiologic evaluations.

6.3.28 Adherence Assessment

At each PK visit in which he/she takes part, each participant will be asked to report on adherence for that day and within the previous 3 days to all the drugs that he/she has been taking (ie, fluconazole, EFV, and/or RIF). See section 10.2 for reporting requirements.

In addition, at all other study visits, all participants will be asked to report adherence to study treatment within the previous 4 days.

## 7.0 CLINICAL MANAGEMENT ISSUES

A5225/HiFLAC sites must follow the DAIDS Table for Grading the Severity of Adult and Pediatric Adverse Events Version 1.0, December 2004, which can be found on the DAIDS DAIDS RSC Web site: <http://rsc.tech-res.com/safetyandpharmacovigilance/>, for grading toxicities related to study treatment.

Toxicity management at non-US CRSs may require reliance on clinical symptoms, clinician judgment, and available laboratory markers, since alternatives to study-provided treatment may be very limited and baseline levels may be different from those in other settings. It is understood that treating physicians will provide whatever available treatment is considered best to protect patient safety and well-being; compliance with study requirements must not compromise such treatment.

This section provides guidelines for management of toxicities related to **study-provided** fluconazole. Management of toxicities thought to be related to ampho B will be according to local standard of care. Guidelines for use of ampho B and management of the most common toxicities associated with it are included in section 5 of the A5225/HiFLAC MOPS and may be consulted, at the discretion of the site investigator.

Participants who permanently discontinue either fluconazole or **any** ampho B**-based regimen** because of an AE should be followed closely until resolution of the AE can be documented.

In the subsections below, ‘interruption’ is used to mean a temporary discontinuation, while ‘discontinuation’ is used to mean a permanent discontinuation. If study-provided fluconazole is interrupted for longer than 3 consecutive days, it must be discontinued and the participant must immediately be treated according to local standard of care (SoC).

The A5225/HiFLAC core team must be notified via e-mail ([[contact]](mailto:[contact])) within 3 business days after premature discontinuation of fluconazole or ampho B in Step 1 or Step 2.

### 7.1 General Toxicities

The management of most fluconazole-related toxicities is summarized in this first section. Management of specific toxicities is addressed in the subsections that follow.

Grades 1 and 2: No change in treatment.

Grade 3 or 4: For a Grade 3 toxicity definitely, probably, or possibly related to fluconazole or for any Grade 4 toxicity, fluconazole should be reduced to 400 mg/day (or 600 mg/day if taking RIF) in Step1 and to 200 mg/day in Step 3. The reduced dose should be administered until toxicity resolves to a Grade ≤ 2 at which time fluconazole may either be escalated [e.g., to 400 mg/day (or 600 mg/day if taking RIF), 800 mg/day, and beyond, up to the assigned dose] or be resumed immediately at the assigned dose, at the discretion of the site investigator.

If the same Grade 3 or 4 toxicity recurs, fluconazole should be interrupted again and the A5225/HiFLAC core team should be contacted ([[contact]](mailto:[contact])).

For a Grade 3 toxicity not related or probably not related to fluconazole, no interruption is necessary.

### Fluconazole-Induced Prolongation in QT Interval

The QT interval has an inverse relationship to heart rate; the measured QT intervals are generally corrected for heart rate in order to determine whether they are prolonged relative to baseline. The site is responsible for documenting any change relative to the baseline value.

Various correction formulae have been suggested, of which the Fridericia’s correction is most widely used. The correction factor used in this protocol is given below.

Fridericia’s correction: QTc = QT/RR0.33, or,

the QT interval divided by the cube root of the RR interval

Grade 1: Fluconazole should continue without interruption, at the discretion of the site investigator.

Grade 2: Fluconazole should continue without interruption, at the discretion of the site investigator. A repeat ECG should be considered 1 week later.

Grade 3: Fluconazole should be interrupted. If the Grade 3 QTc prolongation is considered to be most likely due to concomitant illness or medication, standard management, including discontinuation of the likely causative agent, should be undertaken. If the QTc prolongation resolves to Grade ≤ 1 within 3 days, the investigator should consider whether fluconazole can be re-started, as described in 7.1. If the QTc prolongation does not resolve to Grade ≤ 1 within 3 days, study-provided fluconazole should be discontinued and the participant referred to SoC.

Grade 4: Participants should permanently discontinue fluconazole.

### 7.3 Fluconazole-Induced Hepatotoxicity

Grade 1:     No interruption is necessary.  AST, ALT, alkaline phosphatase, and bilirubin evaluations must be repeated within 1 week.

Grade 2:     No interruption is necessary immediately, however, AST, ALT, alkaline phosphatase, and bilirubin evaluations must be repeated within 3 days. If the lab values are still Grade 2, fluconazole must be dose reduced as described in 7.1. If fluconazole is already being taken at the maintenance dose, it must be interrupted. The lab tests should be repeated within 3 days after dose reduction or interruption.

If the lab values do not decrease to Grade < 2 within 7 days following dose reduction, fluconazole must be discontinued and the participant should be referred to SoC.

If the lab values decrease to Grade < 2 within 7 days, then fluconazole may be restarted or dose-increased as described in section 7.1, at the discretion of the site investigator. AST, ALT, alkaline phosphatase, and bilirubin evaluations must be repeated within 1 week.

Grade 3:     If the toxicity is thought to be possibly, probably, or definitely related to fluconazole, then fluconazole must be interrupted. AST, ALT, alkaline phosphatase, and bilirubin evaluations must be repeated within 3 days.

If any of these lab values are still elevated 3 days following an interruption, fluconazole must be discontinued and the participant referred to SoC.

If the lab values decrease to Grade ≤ 2 within the timeframe noted above that allows for re-start, then fluconazole may be re-started as described in 7.1. AST, ALT, alkaline phosphatase, and bilirubin evaluations must be repeated within 1 week.

Grade 4:     If the toxicity is thought to be possibly, probably, or definitely related to fluconazole, then fluconazole must be interrupted. AST, ALT, alkaline phosphate, and bilirubin evaluations must be repeated within 2 days.

If any of these lab values are still Grade 4 3 days following an interruption, fluconazole must be discontinued and the participant referred to SoC.

If the lab values decrease to Grade ≤ 2 within the timeframe noted above that allows for re-start, fluconazole may be restarted as described in 7.1. AST, ALT, alkaline phosphate, and bilirubin evaluations must be repeated within 1 week.

Among participants with Grade ≥ 3 liver abnormalities in whom fluconazole-associated toxicity is highly unlikely in the opinion of the investigator, fluconazole may be continued without interruption. The investigator should document a definitive alternative etiology if the relationship of toxicity to fluconazole is determined to be highly unlikely.

NOTE: Participants with isolated Grade ≥ 3 hyperbilirubinemia resulting from use of indinavir or atazanavir do not need to have their fluconazole interrupted.

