# GLOSSARY OF STUDY-SPECIFIC TERMS

##### 5FC 5-fluorocytosine

ampho B amphotericin B deoxycholate (in A5225/HiFLAC, the abbreviated name is being used for convenience and is not intended to represent an official name for the drug)

ampho B-based regimen in this study, a regimen that is either ampho B alone or ampho B in combination with 5-fluorocytosine **or fluconazole, according to local standard of care**

CCTG California Collaborative Treatment Group

CM cryptococcal meningitis

CNS central nervous system

CSF cerebrospinal fluid

DLT dose-limiting toxicity: interruption of an induction dose of study-provided fluconazole (i.e., 1200 mg, 1600 mg, or 2000 mg daily) for at least 3 consecutive days as the result of a fluconazole-related toxicity, where the discontinuation was initiated prior to day 14

ECG electrocardiogram

EFV efavirenz

hERG human ether-a-go-go-related gene

HiFLAC High-Dose Fluconazole for Treatment in AIDS-Associated Cryptococcal Meningitis, acronym for A5225

IRIS immune reconstitution inflammatory syndrome

LFCrAg lateral flow cryptococcal antigen (assay)

LP lumbar puncture

MOPS manual of operations

MTD maximum tolerated dose, defined for A5225/HiFLAC as the highest dose of fluconazole that can be safely used [i.e., a dose that results in a ≤ 25% rate of fluconazole dose-limiting toxicity (DLT)].

PML progressive multifocal leukoencephalitis

SIP site implementation plan

SMC study monitoring committee

SoC standard of care

SoE schedule of events (protocol section 6.1)

TEN toxic epidermal necrolysis

TLT treatment-limiting toxicity: a toxicity that results in discontinuation of ampho B-based treatment prior to day 14 and prior to receipt of a total of 8.4 mg/kg ampho B

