## 8.0 CRITERIA FOR PREMATURE TREATMENT OR STUDY DISCONTINUATION

### 8.1 Treatment Discontinuation

- **Failure to have CM confirmed by Day 5 by testing performed at a DAIDS-approved laboratory**
- Fluconazole-related dose-limiting or ampho B-related treatment-limiting toxicity (see section 7.0, Clinical Management Issues or section 5.0, A5225/HiFLAC MOPS).
- Pregnancy or breast-feeding (for fluconazole).
- Interruption of oral fluconazole for any reason for more than 3 consecutive days.
- Requirement for prohibited concomitant medications (see current A5225/HiFLAC MOPS).
- Clinical reasons believed life threatening by the physician, even if not addressed in the clinical management section of the protocol.

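### Section 7.3: a Grade 1–2 liver result at the day-3 retest after a related Grade 3 event meets both the stop rule and the restart rule

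*Protocol*

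**What the plan says.** Protocol section 7.3 sets out management by grade. For a Grade 3 abnormality in AST, ALT, alkaline phosphatase or bilirubin judged possibly, probably or definitely related, fluconazole is interrupted and the tests are repeated within 3 days. Two sentences then decide what follows.

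- Stop: "If any of these lab values are still elevated 3 days following an interruption, fluconazole must be discontinued", with referral to standard of care.
- Restart: "If the lab values decrease to Grade ≤ 2 within the timeframe noted above that allows for re-start, then fluconazole may be re-started", by the steps in section 7.1.

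Section 7.0 fixes the vocabulary for these subsections. An interruption is temporary, while discontinuation "is used to mean a permanent discontinuation". It also sets an outer limit: "If study-provided fluconazole is interrupted for longer than 3 consecutive days, it must be discontinued". Section 8.1 repeats that limit as a criterion for ending treatment: "Interruption of oral fluconazole for any reason for more than 3 consecutive days".

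Section 4.1.13 admits participants with AST, ALT and alkaline phosphatase up to 5 times the upper limit of normal, and total bilirubin up to 2.5 times.

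**The concern.** The stop sentence turns on whether a value is elevated, and the restart sentence turns on its grade. Grades 1 and 2 satisfy both. At the day-3 retest the same laboratory report therefore supports a mandatory permanent stop and an optional restart, and sites could reasonably act differently on it.

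What is at stake is treatment and how it is recorded:

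- Discontinuation of study-provided fluconazole is a primary outcome (section 9.2.1.1).
- A participant off study treatment cannot enter Step 3 or Step 4 (sections 4.6.2 and 4.8.1) and has no further study-required CSF cultures (section 6.3.22).
- One of the bases for the Stage 2 sample size (section 9.3.2) is a culture-negativity proportion in which early discontinuation counts as failure. Under that definition, a stop made only because of this wording could be scored as lack of efficacy.

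**Working it through.** The point is textual and there is no plan figure to reproduce. The check applies the two Grade 3 sentences to each possible result at the 3-day point.

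| Worst value at day 3 | Stop sentence (elevated) | Restart sentence (Grade ≤ 2) | Outcome as written | Outcome if the stop sentence read Grade ≥ 3 |
| --- | --- | --- | --- | --- |
| Normal | not met | met | restart allowed | restart allowed |
| Grade 1–2 | met | met | must stop and may restart | restart allowed |
| Grade 3 or higher | met | not met | stop | stop |

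Only the middle row collides. With the proposed wording the two conditions are complementary, with no overlap and no gap.

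**Timing.**

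1. Result at Grade 1–2 before day 3: the stop sentence speaks of the position 3 days after interruption, so only the restart sentence applies.
2. Result at Grade 1–2 on day 3: both apply. The retest is due within 3 days, so day 3 is a permitted retest day.
3. Drug still withheld beyond day 3: sections 7.0 and 8.1 end treatment whatever the grade, consistently with the stop sentence.

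The conflict is therefore confined to a deciding result at the 3-day point.

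**Comparison with neighbouring rules.**

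- The Grade 2 rule in section 7.3 uses one threshold on both sides: below Grade 2 within 7 days allows restart or increase, and otherwise the drug is discontinued.
- The Grade 4 stop sentence names Grade 4.
- The Grade 3 QTc rule allows restart at Grade 1 or below and otherwise says: "If the QTc prolongation does not resolve to Grade ≤ 1 within 3 days, study-provided fluconazole should be discontinued". One threshold serves both directions, so its sentences cannot overlap.
- The Grade 3 liver stop sentence is the only stop rule in section 7.3 without a grade.

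**Raised baseline.** A participant may enter with enzymes above normal but within the limits of section 4.1.13. After a related Grade 3 rise, a return to that entry value by day 3 is full recovery for that person, yet the value is still elevated. Read literally, the stop sentence ends study fluconazole permanently.

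**DLT counts.** The Glossary defines a DLT as an interruption of an induction dose "for at least 3 consecutive days as the result of a fluconazole-related toxicity, where the discontinuation was initiated prior to day 14". Take a retest 3 days after interruption to mean that 3 consecutive days have been missed. An interruption begun before day 14 is then already a DLT at the decision point, whichever sentence the site follows. One begun on or after day 14 is not a DLT under either. The count is the same both ways.

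**The case against.** The strongest reply is that context supplies the meaning. The sentence sits under the Grade 3 label, follows a Grade 3 trigger and is followed at once by a restart rule at Grade 2 or below. The parallel Grade 4 paragraph names its own grade. A sensible clinician would read it as still at Grade 3 or worse. That is very likely the intent, and on that reading the conflict disappears. But the mandatory sentence does not say it, and the correction simply writes the intent down.

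A second reply is that a *must* and a *may* are not strict opposites: a site that stops breaches neither sentence. That is correct. It means the literal text resolves towards stopping, which permanently removes participants whom the next sentence treats as recovered enough to resume. Section 7.0 calls these provisions guidelines and leaves room for clinical judgement, which softens the problem but does not make sites consistent.

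The limits on the consequences also stand. Participants who stop treatment are still followed on study (section 6.2.4). Later cultures are lost only for those whose previous culture was positive. The core team hears of Step 1 or Step 2 discontinuations within 3 business days, although by then the drug has been stopped.

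A reader might infer a second contradiction from section 8.1, which lists "Fluconazole-related dose-limiting or ampho B-related treatment-limiting toxicity" as a reason to end treatment, because a 3-day interruption begun before day 14 is a DLT that section 7.3 might allow to restart. The documents do not support making this a separate error: the bullet refers back to section 7.0, and what remains is at most a missing statement of precedence. A reader might also count scheduled chemistry visits after day 14 to gauge frequency. Those visits are not the unscheduled 3-day retests that create the conflict, and they are not events. Nor does the Grade 4 paragraph need a matching edit: a Grade 3 value there on day 3 does not qualify for restart, and continued interruption is ended by sections 7.0 and 8.1.

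**Conclusion.** The wording is wrong in one narrow case: a related Grade 3 liver abnormality whose deciding retest falls at day 3 and shows Grade 1–2. In that case section 7.3 requires permanent discontinuation and permits restart. Severity is minor.

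The number affected is probably small and cannot be estimated from the protocol, so no rate is given. It would be too strong to infer that dose escalation or the MTD is compromised: DLT classification is the same under either sentence, and section 5.1 describes Stage 1 as completed. The remaining effect is on management in Stage 2 and on who is recorded as having discontinued.

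Two assumptions carry this. *Elevated* has its ordinary meaning of above normal, since the protocol gives no other. A day-3 retest is taken to mean 3 full consecutive days of missed dosing, which is what makes the DLT count neutral.

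**What to change.** In the Grade 3 paragraph of section 7.3, change the stop condition from *still elevated* to *still Grade ≥ 3*, so that it is the exact complement of the restart threshold. A participant back at a raised but admissible baseline of Grade 2 or below would then be eligible for restart at the investigator's discretion.

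The cost is one phrase, issued by clarification memo or in the amendment already planned before Stage 2. Sample size, visits, data collection and the escalation rule are untouched.
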